### Process Evaluation

After the peer support intervention (between 4 and 12 weeks post childbirth), an approximate purposive sample of 20 mothers, 10 each from intervention and control groups (actual number will depend upon data saturation), and all (N=20) peer support volunteers will be selected to participate in the interview to obtain their opinions and comments on the receipt and delivery of the peer support intervention program, respectively. Participation in the interviews will be voluntary. The process evaluation of each interview will take approximately 30-60 min. Participants will be given pseudonyms during the interviews to protect their actual identities. As part of the presentation of the results, their own words will be used in text and will be made anonymous. The interview will be audio-recorded and transcribed into text form. The recruitment will continue until the proposed number is achieved or data saturation is achieved, whichever occurs earlier.

### Outcome Measures and Instruments

The demographic data of mothers (eg, age, gender, ethnicity, education) will be collected. The following instruments will be used to measure the outcomes.

#### Edinburgh Postnatal Depression Scale

The Edinburgh Postnatal Depression Scale (EPDS) [65] is a 10-item scale that has been widely used to measure postnatal depression in international [66,67] and local studies [24,68]. On the basis of previous trials [61,69], the recommended cutoff score of 9 will be used to screen the mothers. A score of >13 is recommended to be used as probable diagnosis for PND. The sensitivity of EPDS ranged from 68% to 80% with specificity of 77% and Cronbach alpha of .88 [65].

#### Patient Health Questionnaire

The Patient Health Questionnaire (PHQ-9) [70] is a shortened 9-item questionnaire extracted from the full PHQ used to diagnose and measure the severity of major depression. It is scored from 0 to 27, with higher scores indicating high severity. An additional item was added to the diagnostic portion for patients who indicated on the questionnaire that they faced problems: “How difficult have these problems made it for you to do your work, take care of things at home, or get along with other people?” The PHQ-9 is well tested and validated in international [71,72] and local [73] studies. The Cronbach alpha in a previous local study was .87 [73].

#### State Trait Anxiety Inventory

The State Trait Anxiety Inventory (STAI) [74] is a 40-item, self-administering 4-point Likert scale used to assess parental anxiety state. This instrument is well tested for its psychometric properties in international [75-77] and local setting [78]. The Cronbach alpha value of the instrument is .8 in local setting [78].

#### University of California, Los Angeles Loneliness Scale

The University of California, Los Angeles (UCLA) Loneliness scale [79] is a 10-item self-report instrument used to measure loneliness. Items are rated on a 4-point Likert-type scale to produce a summative score ranging from 10 to 40, with higher scores indicating higher degrees of loneliness. In a previous study, the Cronbach alpha value was .90 [61].

#### Perceived Social Support for Parenting

This 4-item instrument developed by Leerkes and Crockenberg [80] will be used to measure the satisfaction of parents with the social support from partners and from others. The 5-point scale ranges from 5 to 20 each for the support received from partners or others. The instrument has shown high internal consistency with Cronbach alpha value of .81 in a previous study [80].

A semistructured interview guide will be used for process evaluation. Individual telephone or face-to-face interviews with mothers and peer volunteers will be conducted (4-12 weeks post childbirth) to identify the strengths, weaknesses, and effectiveness of the intervention (from the mothers’ and peer volunteers’ perspectives) as well as on the delivery process from the peer volunteers. All interviews will be audio-recorded.

### Study Procedure

The study will be composed of 2 phases:

Phase 1: Planning intervention strategies for intervention group, including recruitment of peer volunteers, development of peer volunteer training manual, and training the peer volunteers.

Phase 2: Implementing the PIP and investigating its effectiveness on maternal outcomes.

The recruitment of peer volunteers in phase 1 was conducted before the recruitment of participants. Recruitment was done through the blasting of emails to the study venue working community and through word of mouth. On the basis of a previous study [61], 20 peer volunteers were recruited. The recruitment of ethnically diverse peer volunteers was ensured by RA1. RA1 (1) coordinated the peer volunteer recruitment and acquired their informed consent, (2) participated in peer volunteer training sessions, (3) has been pairing mothers with a suitable peer volunteer based on the availability of the volunteer, (4) monitoring the intervention implementation, (5) providing support to peer volunteers as required, and (6) assisting in setting up peer volunteer meetings.

Peer volunteers were required to attend a 4-hour training session conducted by the psychiatrist (one of the study team member). The training for all recruited volunteers was completed in one session in June 2017 to maintain standardization. The training session included roleplaying and discussions to provide necessary skills for the peer-volunteers to successfully deliver the intervention. Peer volunteers were also trained in assessing and conducting the appropriate referrals to relevant health care professionals should the need arise. A peer volunteer training manual was distributed during training to facilitate and guide the intervention process. The trial was introduced during training sessions, and all peer volunteers who agree to participate were required to fill a demographic form and were provided activity logs to account for their sessions with the mothers.

For phase 2, ethics approval has been granted (NHG DSRB: 2017/00815), and participant recruitment has commenced in the postnatal clinics at the study venue. RA1 has informed the nurse managers and clinicians of the respective postnatal wards of the study. The nurse in charge creates a short list of eligible participants based on the selection criteria and verifies the overall physical and psychological well-being of the women. RA1 then approaches those women who meet the inclusion criteria and explains the study purpose and details to them. Voluntary participation is emphasized. Those who are keen to participate are screened using EPDS. On the basis of previous studies [60,61], only mothers with an EPDS score of at least 9 are recruited. After RA1 obtains their written consent, the participants are randomized and grouped into the intervention or control groups accordingly. Participants are then asked to fill a baseline questionnaire, a demographics form, as well as to provide their name and contact information for future data collection and correspondence purposes.

### Data Collection

A single-blinded technique is used. Research assistant two (RA2), who is not part of the randomization and is not involved in the intervention, collects all data and will conduct the process evaluation interviews to avoid bias. Outcome measures of depression, anxiety, loneliness, and perceived social support are collected by RA2 primarily through a Web-based questionnaire, unless the mothers request for an alternative mode, such as through phone call, face-to-face, or via mail. Follow-up time points for all mothers are as follows: (1) immediately after the post birth when discharged from the hospital (baseline), (2) 4 weeks postpartum, and (3) 12 weeks postpartum. Between week 4 and week 12 postpartum, RA2 will invite mothers each from the intervention and control groups to participate in a semistructured process evaluation interview either face-to-face or by telephone. Participation is strictly voluntary. RA2 will also conduct process evaluation interviews with peer volunteers once they are done administering technology-based support to the assigned mothers. The activity logs will also be collected by RA2 for further evaluation. The PND at 12 weeks is chosen as the primary outcome because the results suggest that most PND develop within this time period [19], and we hope to give value to other PND prevention trials [48,49,81-83] by providing comparable results. The 4-week period is chosen for data collection because most of the mothers will be ending their confinement practices, which may alter their support needs [58]. The consolidated standards of the reporting trial flowchart are presented in Figure 2.

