### Gaps in the Literature

The scarcity of resources and advancement of technology has led to an increasing trend in telemedicine, which is a previously underutilized platform in the health care sector [51-55]. Technology-based interventions are not only accessible and cost-effective; they also enhance privacy, flexibility, and reduce stigmatization [56,57]. These interventions are especially important for a multiracial, conservative society, such as Singapore, where traditional views and homebound confinement practices restrict new mothers from seeking the necessary help after childbirth [58,59]. Therefore, technology-based support will be the most practical alternative form of support for local mothers. Previous studies have successfully implemented technology-based support intervention for new mothers [51,60]. Technology-based peer support has effectively helped mothers maintain breastfeeding for 3 months postpartum as compared with those in the control group [60]. In another technology-based peer support study [51], pregnant mothers who received support were shown to have decreased anxiety and depressive traits. The risk of PND was also reduced to half of those in the control group. From these studies, we can deduce that the use of technology-based support may be effective in reducing the risk of depression for high-risk mothers.

The aim of this study is to examine the effectiveness of a technology-based peer support intervention program among mothers at risk for postnatal depression in the early postpartum period. This study has 3 objectives:

To evaluate the peer support intervention program on maternal outcomes, including PND (primary outcome), anxiety, loneliness, and social support (secondary outcomes)To analyze mothers’ evaluations of their peer support experienceTo analyze peer volunteers’ evaluations of their peer support experience

We hypothesized that when compared with those in the control group receiving routine care, mothers receiving the peer support intervention program will report a significantly lower level of PND, lower level of anxiety, lower level of loneliness, and higher level of social support received.

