### Data Analysis

All quantitative data will be analyzed using the latest version of IBM SPSS. Missing data will be replaced for intention-to-treat analysis. Both intention-to-treat and per-protocol analyses will be conducted to compare the differences between groups. Descriptive statistics, such as mean, standard deviation, and range for continuous data and frequency as well as percentages, will be used for the nominal and ordinal data. Cronbach alpha value will be used to examine the internal consistency of the questionnaires. Inferential statistics, such as independent sample *t* test or analysis of variance (ANOVA), will be used to compare outcome differences among or between the demographic subgroups. Presuming that the outcomes are normally distributed, parametric tests will be used. Repeated measures analysis of covariance (ANCOVA) adjusted for confounding variables (eg, age, education level) will be used to test the effect of intervention on outcomes, including postnatal depression, anxiety, loneliness, and social support across 3 time points in the data collection. The percentage changes in the postnatal depression, anxiety, loneliness, and social support scores from baseline will be calculated for repeated measures ANCOVA. The ANCOVA will be used to test the differences in each outcome among 2 groups at 2 posttests separately.

Qualitative data from the interviews will be analyzed using the thematic analysis [84,85]. The audio interview data will be transcribed verbatim by RA2 concurrently with data collection to capture nonverbal information. Transcribed data will then be sorted into different categories, with similar ideas in a category highlighted in the same color. Related codes or categories will be collated to form subthemes, which will be reviewed and combined to form overarching themes [84] that will describe the opinions of mothers on strengths and weaknesses of the intervention and ways to improve the intervention or on the routine postnatal care. A total of 2 investigators will be involved in the analysis process and will compare and discuss the categories, subthemes, and themes generated and achieved in the consensus. Rigor or trustworthiness, including credibility, transferability, dependability, and conformability, will be considered in the study process [85].

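### The primary outcome, postnatal depression at 12 weeks, is tied to no single scale, test or analysis population, so more than one result could be claimed as primary

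*Protocol article*

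**What the plan says.** **Outcome.** The objectives, at the end of Gaps in the Literature, rank the constructs: "maternal outcomes, including PND (primary outcome), anxiety, loneliness, and social support (secondary outcomes". The hypothesis there is that mothers in the intervention group "will report a significantly lower level of PND, lower level of anxiety, lower level of loneliness, and higher level of social support received", with no scale or time given. Data Collection adds the time: "The PND at 12 weeks is chosen as the primary outcome".

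**Scales.** Outcome Measures and Instruments introduces all its questionnaires as measures of the outcomes. Two of them measure depression. EPDS "is a 10-item scale that has been widely used to measure postnatal depression in international" and local studies. PHQ-9 is "used to diagnose and measure the severity of major depression". Neither is ranked, and no other named outcome would use PHQ-9.

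**Tests.** Data Analysis assigns the test of the intervention effect to a repeated measures ANCOVA "across 3 time points in the data collection", and says that percentage changes from baseline will be calculated for that model. It then adds: "The ANCOVA will be used to test the differences in each outcome among 2 groups at 2 posttests separately".

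**Populations.** "Both intention-to-treat and per-protocol analyses will be conducted to compare the differences between groups". Neither is called primary.

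**Sample size.** Sample Size Determination uses a two-sample t test with a standardised effect of 0.6, 80% power and two-sided 5%. This gives 45 per group, raised to 59 per group (118 in total) for dropout. It refers to outcome variables in general, with no scale or time point.

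**The concern.** A confirmatory claim needs one named result: one score, one time, one comparison, one set of mothers. This plan fixes the construct and the time and leaves the other parts open. Once the data are in, a significant EPDS result at week 12, a significant PHQ-9 result at week 12 or a significant repeated measures test could each be presented as confirming the primary hypothesis. The 5% level and 80% power in the sample size section describe a single test, and nothing says which of the planned tests that is.

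There is also a mismatch between two stated parts of the plan. Data Collection selects week 12 and gives a reason for it. Data Analysis gives the test of the intervention effect first to a model spanning all three time points. That model answers a different question from the difference between groups at week 12.

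**Working it through.** **1. The plan's own figure.** Inputs from Sample Size Determination: d = 0.6, two-sided 5%, 80% power, equal groups. The noncentral t calculation gives 44.6, so 45 per group, with 80.4% power at 45. For dropout, 45 × 1.3 = 58.5, rounded up to 59, and 2 × 59 = 118. The stated 45 and 118 reproduce for one test at 5%.

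**2. What is fixed and what is open for the primary result.**

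| Element | Fixed? | Where |
|---|---|---|
| Construct: postnatal depression | yes | Gaps in the Literature |
| Time: 12 weeks | yes | Data Collection |
| Scale: EPDS or PHQ-9 | no | Outcome Measures and Instruments |
| Test: repeated measures ANCOVA or week-12 ANCOVA | no | Data Analysis |
| Population: intention to treat or per protocol | no | Data Analysis |

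**3. Error rate if either scale at week 12 may count.** Let Z1 and Z2 be the two test statistics under no effect, with correlation ρ taken equal to the between-scale correlation. The documents give no ρ, so a range is assumed. The chance of at least one false positive is 1 − P(|Z1| ≤ 1.96 and |Z2| ≤ 1.96):

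- ρ = 0.6: 8.8%
- ρ = 0.7: 8.3%
- ρ = 0.8: 7.8%
- independent tests, for reference: 1 − 0.95² = 9.75%

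If the repeated measures test on either scale also counts, there are four routes and the figure rises. For independent tests it would be 1 − 0.95⁴ = 18.5%. These tests are positively correlated, so the true value lies below that. I give no single figure, because the plan does not say which term of the model would be read.

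**4. Is the repeated measures test the week-12 contrast?** Percentage change is zero at baseline for every mother. Averaged over three visits, the outcome is (0 + c4 + c12)/3, where c4 and c12 are the changes at weeks 4 and 12. This equals two thirds of the mean of c4 and c12. The group term therefore compares the average of the two posttest changes. The group-by-time term is an omnibus test over visits. Neither isolates week 12.

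**5. Power of one designated week-12 test.** For ANCOVA with baseline-to-week-12 correlation r (assumed), the effective standardised effect is 0.6/√(1 − r²). At 45 per group:

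- r = 0.3: 0.6/√0.91 = 0.629, power 84%
- r = 0.5: 0.6/√0.75 = 0.693, power 90%
- r = 0.7: 0.6/√0.51 = 0.840, power 98%

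At r = 0 it falls back to about the 80% of the t test. Because entry requires an EPDS of at least 9, the range of baseline scores is restricted, so the lower part of this range is plausible.

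**6. The alternative of keeping both scales as primary.** At 2.5% each, 80% power needs 55 evaluable per group by the noncentral t calculation. At 45 per group the power is 71%.

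**The case against.** **EPDS is the natural reading.** It is the only scale described as measuring postnatal depression, it carries the cutoff for probable diagnosis, and it is the entry screen. PHQ-9 is described in terms of major depression. This makes EPDS the likelier intended measure. It does not settle the matter, because PHQ-9 stands in the same list of outcome instruments, without rank and with no other outcome to serve.

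**Hierarchy is SAP detail.** Test ranking and alpha allocation are often left to a full protocol or SAP, which are not shown, and silence on them would be no finding. A per-protocol analysis beside intention to treat is also routine. Both points stand. What remains is stated text: the article selects week 12 and then describes an effect test that is not the week-12 comparison, beside one that is.

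**Sizing by t test and analysing by ANCOVA is ordinary practice.** That is correct, and it is not criticised here.

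**Stronger readings that the document does not support.**

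- A reader might infer that including baseline as a visit dilutes the effect and costs power. That needs raw scores averaged over three visits. The plan uses percentage change, and the constant zero at baseline scales the group difference and its standard deviation by the same two thirds, so the group test is unchanged. With absolute change standing in for percentage change and an effect of 0.6 at both posttests, the variance of the mean change at r = 0.5 is (1 + 0.5)/2 + 1 − 2 × 0.5 = 0.75. Then d = 0.693 and power is 90%, equal to the week-12 ANCOVA. Over r = 0.3 to 0.7 it is 78% to 99%.
- A reader might count the separate 4-week tests as further chances at the primary claim. Data Collection fixes week 12 and gives its own reason for the 4-week visit.
- A reader might say that every test is run at 5%. That level appears only in the sample size section; Data Analysis states none.

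**Conclusion.** The point holds in a limited form. The plan names a primary construct and time but ties them to no one scale, test or population, and its repeated measures test is not the week-12 contrast. If either depression scale at week 12 may be claimed as primary at 5%, the false-positive chance is about 8-9%, for an assumed between-scale correlation of 0.6-0.8. It is higher if the repeated measures test is also eligible.

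The planned power is unassigned, not shown to be lost: a designated week-12 ANCOVA meets or exceeds 80% on the plan's own inputs. The population issue is minor, and amounts only to neither set being called primary. The point should be settled before the data are analysed, but it does not put the trial size or conduct in question.

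**What to change.** State one primary analysis: EPDS total score at 12 weeks, all mothers as randomised, ANCOVA adjusted for baseline EPDS, two-sided 5%. An equivalent choice is the 12-week contrast from a model on the two posttests with baseline as a covariate. Use the score itself with baseline as a covariate in place of percentage change.

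Label PHQ-9, the 4-week results and the repeated measures test as secondary, and the per-protocol results as supportive.

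This is one paragraph, written before analysis. It needs no new data, since baseline is already collected, and the target of 118 is unchanged. The Results section reports 73 of 118 mothers recruited, so it could still be prespecified at that stage. The price is that a favourable PHQ-9 result can no longer rescue a negative EPDS result. If the sponsor wants both scales as alternative primaries, the level must be split, at the cost shown in step 6 of the working.

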**Figure 2 figure2:**
[figure not shown]
Consolidated Standards of Reporting Trial Flowchart. EPDS: Edinburg Postnatal Depression Scale; PHQ-9: Patient Health Questionnaire 9; STAI: State Trait Anxiety Inventory; UCLA: UCLA Loneliness Scale; PSSP: Perceived Social Support for Parenting.

### Data Analysis

All quantitative data will be analyzed using the latest version of IBM SPSS. Missing data will be replaced for intention-to-treat analysis. Both intention-to-treat and per-protocol analyses will be conducted to compare the differences between groups. Descriptive statistics, such as mean, standard deviation, and range for continuous data and frequency as well as percentages, will be used for the nominal and ordinal data. Cronbach alpha value will be used to examine the internal consistency of the questionnaires. Inferential statistics, such as independent sample *t* test or analysis of variance (ANOVA), will be used to compare outcome differences among or between the demographic subgroups. Presuming that the outcomes are normally distributed, parametric tests will be used. Repeated measures analysis of covariance (ANCOVA) adjusted for confounding variables (eg, age, education level) will be used to test the effect of intervention on outcomes, including postnatal depression, anxiety, loneliness, and social support across 3 time points in the data collection. The percentage changes in the postnatal depression, anxiety, loneliness, and social support scores from baseline will be calculated for repeated measures ANCOVA. The ANCOVA will be used to test the differences in each outcome among 2 groups at 2 posttests separately.

Qualitative data from the interviews will be analyzed using the thematic analysis [84,85]. The audio interview data will be transcribed verbatim by RA2 concurrently with data collection to capture nonverbal information. Transcribed data will then be sorted into different categories, with similar ideas in a category highlighted in the same color. Related codes or categories will be collated to form subthemes, which will be reviewed and combined to form overarching themes [84] that will describe the opinions of mothers on strengths and weaknesses of the intervention and ways to improve the intervention or on the routine postnatal care. A total of 2 investigators will be involved in the analysis process and will compare and discuss the categories, subthemes, and themes generated and achieved in the consensus. Rigor or trustworthiness, including credibility, transferability, dependability, and conformability, will be considered in the study process [85].

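### Percentage change from baseline is a poor response for the repeated measures ANCOVA; raw scores adjusted for baseline should replace it

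*Protocol article*

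**What the plan says.** All of the following is in the protocol article.

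- **Model for the intervention effect (Data Analysis):** "Repeated measures analysis of covariance (ANCOVA) adjusted for confounding variables (eg, age, education level) will be used to test the effect of intervention on outcomes". The model is said to run "across 3 time points in the data collection".
- **Response for that model (Data Analysis):** "The percentage changes in the postnatal depression, anxiety, loneliness, and social support scores from baseline will be calculated for repeated measures ANCOVA".
- **A second analysis (Data Analysis):** "The ANCOVA will be used to test the differences in each outcome among 2 groups at 2 posttests separately". Neither its response scale nor a baseline covariate is stated.
- **Distribution (Data Analysis):** "Presuming that the outcomes are normally distributed, parametric tests will be used".
- **Scales (Outcome Measures and Instruments):** for PHQ-9, "It is scored from 0 to 27, with higher scores indicating high severity"; for UCLA, "a summative score ranging from 10 to 40". The social support scale (PSSP) is given as 5 to 20 for each source of support.
- **Entry (Study Procedure):** mothers need an EPDS of at least 9. PHQ-9 has no entry threshold.
- **Primary outcome (Data Collection):** postnatal depression at 12 weeks.

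**The concern.** The choice of response is stated, so it is not a detail left to a fuller document. Percentage change divides each mother's change by her own noisy baseline. This causes four difficulties:

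1. At a baseline of 0 the quantity does not exist.
2. At small baselines it becomes very large upwards, but it can never fall below -100%. The distribution is then skewed, against the normality presumption.
3. On a scale whose minimum is not zero, the result depends on where the scoring convention puts the origin, which has no clinical meaning.
4. At the baseline visit it equals 0 for everyone, so only two of the three time points carry information.

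At stake are the interpretability of the estimated effect, its precision on the scales with small baselines, and a clear treatment of fully observed mothers whose ratio cannot be computed.

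**Working it through.** **1. The plan's own figure.** Sample Size Determination uses a two-sample t test, effect size 0.6, 80% power and 5% two-sided. The normal approximation gives n = 2 × (1.96 + 0.842)² / 0.6² = 43.6, so 44 per arm. The exact t calculation gives 44.6, so 45 per arm with power 0.804. The stated 45 reproduces. It refers to a standardised difference in means, with no allowance for a percentage-change response.

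**2. Zero and small baselines (PHQ-9, 0 to 27).**
- Baseline 0: (y − 0)/0 is undefined.
- 1 to 4: (4 − 1)/1 = +300%.
- 12 to 3: (3 − 12)/12 = −75%.

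A 3-point worsening thus counts four times as much as a 9-point improvement.

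**3. Non-zero floors.** UCLA runs from 10 to 40. Scoring the same answers from 0 subtracts 10 from every total:

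| UCLA change | % change, 10–40 scoring | % change, 0–30 scoring |
|---|---|---|
| 12 to 11 | −1/12 = −8.3% | −1/2 = −50% |
| 20 to 15 | −5/20 = −25% | −5/10 = −50% |
| 36 to 27 | −9/36 = −25% | −9/26 = −34.6% |

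The last two mothers are equal on one scoring and unequal on the other. The same applies to PSSP: 10 to 8 is −2/10 = −20% as scored, and −2/5 = −40% measured from its floor of 5. A difference in points is unaffected by the choice of origin.

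**4. Time points.** At baseline, (b − b)/b = 0 for every mother with b > 0. A percentage-change model therefore has two informative occasions, weeks 4 and 12.

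**5. Power.** The article gives no baseline means, SDs or correlations, so every input here except the 0.6 SD effect and the 45 per arm is an assumption. Simulation: one posttest, 45 per arm, shift of 0.6 SD, 4,000 trials per setting, scores rounded and confined to the scale range. Zero-baseline mothers were dropped from the percentage-change analysis as a device of the calculation. Each cell gives power for percentage change without a baseline covariate, then for the raw score adjusted for baseline.

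| Scale (assumed mean, SD) | r = 0.3 | r = 0.5 | r = 0.7 | Loss, points |
|---|---|---|---|---|
| PHQ-9 (7, 4.5) | 0.43 v 0.82 | 0.57 v 0.89 | 0.80 v 0.97 | 40, 32, 17 |
| PHQ-9 (5, 4) | 0.43 v 0.80 | 0.57 v 0.87 | 0.79 v 0.96 | 37, 30, 17 |
| UCLA (20, 5) | 0.61 v 0.83 | 0.77 v 0.90 | 0.94 v 0.98 | 21, 13, 3 |
| EPDS, cut at ≥9 (11, 4 before the cut) | 0.78 v 0.83 | 0.87 v 0.89 | 0.97 v 0.97 | 5, 3, 1 |

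(Losses are taken from unrounded powers.) About 7% of mothers had an undefined PHQ-9 ratio in the first setting and 13% in the second.

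**6. How much is due to the missing baseline covariate?** When the baseline score was added to the percentage-change model in the same simulations, the loss was 16 to 33 points on PHQ-9, 1 to 5 on UCLA and 1 to 2 on EPDS. Most of the UCLA loss therefore comes from not adjusting for baseline. Most of the PHQ-9 loss comes from the ratio itself.

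**7. Sensitivity to the assumed distribution.** A second simulation used a negative binomial PHQ-9 (mean 5 to 9, SD 4 to 5) and 41 per arm, about what remains of 118 after 30% dropout (118 × 0.7 / 2 = 41.3):
- r = 0.3: 48–54% v 71–78%.
- r = 0.5: 66–73% v 77–85%.
- r = 0.7: no loss.

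Zero baselines made up 0.5% to 7%, and the median skewness of percentage change was 1.3 to 2.6. For EPDS cut at ≥9 with 41 per arm, power was 77/83/89% v 79/83/91% at r = 0.2/0.4/0.6, a loss of 0 to 2 points.

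**The case against.** Several points on the other side have weight.

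- **EPDS is largely protected.** With entry at 9 or more, zero or tiny denominators should not arise. If postnatal depression is measured by EPDS, the primary comparison is barely affected. This stands.
- **PHQ-9 may not be in this model.** Data Analysis names postnatal depression, which the article links to EPDS, and does not name PHQ-9. PHQ-9 is described as measuring major depression, though Data Collection lists depression among the outcomes. The PHQ-9 consequences are therefore conditional.
- **The separate posttest ANCOVAs may already use raw scores** and would give a 12-week comparison directly. That is possible but not stated, and it would leave the repeated measures model unchanged. A reader might call the repeated measures ANCOVA the main model, but the article ranks neither.
- **The covariates are examples.** The model is "adjusted for confounding variables (eg, age, education level) will be used to test the effect of intervention". A reader might infer that baseline adjustment has been rejected. An illustrative list in a condensed article does not show that.
- **Three time points** may only mean that three collections are needed to form two changes. The wording fits poorly, but it is not a firm contradiction.
- **Exclusion of zero-baseline mothers** might be inferred as a breach of intention-to-treat. The article does not say they would be dropped; it says missing data will be replaced. It gives no rule for a ratio that is undefined although both scores were observed.
- **Comparability with other trials** is not lost altogether, since means and SDs are also planned and point differences can be derived from them.

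None of this defends percentage change as the response in an inferential model.

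**Conclusion.** The point holds as a should-fix. The article commits to a response that is undefined at zero, skewed at small baselines and dependent on the scoring origin for UCLA and PSSP. These facts follow from the stated ranges and need no assumption.

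The size of the power loss does rest on assumed means, SDs and correlations. It is roughly 0 to 40 points on PHQ-9 (if analysed), 3 to 21 on UCLA when no baseline covariate is used, and about 0 to 5 on EPDS. The EPDS figure also assumes that the baseline score, like the screening score, is at least 9.

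A reader might conclude that the primary result is compromised. The documents do not support that: harm to an EPDS-based primary outcome is small.

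**What to change.** Drop percentage change as the response in the inferential model. In both the repeated measures ANCOVA and the separate posttest ANCOVAs, analyse the raw total scores at 4 and 12 weeks, with the same instrument's baseline score as covariate alongside the planned ones such as age and education. Report the adjusted mean difference in points with its 95% CI. Keep percentage change, if wanted, as a descriptive summary only.

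The baseline and follow-up scores are already being collected, so the cost is a change of wording in the analysis plan, made before the data are analysed. No extra mothers are needed. At effect size 0.6, a baseline-adjusted comparison needs about 41, 34 or 24 per arm at r = 0.3, 0.5 or 0.7, using effect size 0.6/√(1 − r²) in the t calculation, against 45 without adjustment.
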